### Primary outcome

#### CMS

The CMS, the most commonly used to assess pain and disability in patients with shoulder complaints [16], will be employed to measure the shoulder-specific scoring in the study. It consists of 100 points, including pain (15 points), activities of daily living (20 points), strength (25 points), and ROM: forward elevation, external rotation, abduction, and internal rotation of the shoulder (40 points); the higher the shoulder score, the better the shoulder function is [20]. The CMS has been confirmed to have good reproducibility (ICC = 0.827), reliability (Cronbach’s *α* = 0.739), and construct validity [16]. The research assistants assist the participants in completing the items and obtaining the final score.

### Secondary outcomes

#### VAS

The VAS score, a basic self-reported measure for assessing pain intensity, will be used in this investigation. It is a horizontal line of 100 mm, with 0 mm (the left endpoint) denoting no pain and 100 mm (the right endpoint) indicating excruciating pain [17]. The participants will be requested to choose the location on the line that best indicated their pain level. Furthermore, participants will be advised to measure the intensity of the primary pain for 4 times: overall pain intensity and pain intensity at rest, at night, and during movement.

#### ROM

ROM will be measured in degrees using a goniometer. The ROM measurement protocol will be based on a previous study [18] and include flexion–extension, isolated abduction, neutral external rotation, and internal rotation.

#### SF-36

The SF-36 will be used to evaluate the participants’ quality of life. This health survey questionnaire is a standardized, well-researched, self-reporting health measure scoring ranged from 0 (poor health) to 100 (good health), which includes 36 questions covering eight health domains [19].

### Participant timeline {13}

As shown as Table 2, participants in FSM and SM both groups are treated up to 4 weeks based on the interventions of each group, in parallel, participants in each group performed exercises at home for 12 weeks. For the follow-up time points, the participants will be assessed at baseline and 4, 12, 18, and 24 weeks.

**Table 2 Tab2:**
[figure not shown]
Schedule of enrolment, interventions, and assessment

*FSM* Five-step shoulder manipulation, *SM* Sham manipulation, *CMS* Constant-Murley score, *VAS* Visual analog scale, *ROM* Range of motion, *SF-36* 36-item short form survey

### Sample size {14}

The sample size is calculated based on our preliminary study, which was completed from November 2021 to February 2022. The prior research compared CMS changes from baseline to the end of 4-week treatment in patients receiving FSM or SM plus home-based exercise. Our previous results showed that CMS increased by 24.32 (μ_r_) in the FSM group and increased by 10.31 (μ_c_) in the SM group, and the standard deviation of the FSM group was 17.84 (*σ*). On the basis of the above data, when 1/3 of the standard deviation of the FSM group is selected for Δ, *α* = 0.025 (single-sided), *Z*_1−0.025_ = 1.96, 1 – *β* = 0.90, *Z*_1−0.10_ = 1.282, and the ratio of the number of subjects between the FSM group and SM group (*K*) = 1, using the following formula, 104 participants are required for each group: $${n}_{c}=\frac{{{\left({Z}_{1-\alpha }+{Z}_{1-\beta }\right)}^{2}\sigma }^{2}\left(1+\frac{1}{K}\right)}{{\left({\mu }_{r}-{\mu }_{c}-\Delta \right)}^{2}}$$$${n}_{r}={Kn }\ _{c}$$

On this basis, considering an estimated dropout rate of 20%, 125 cases will be needed for each group. Additionally, because there are three trial centers in this study, 15 additional cases are required for each group owing to the multicenter design. Therefore, a total of 280 participants will be enrolled in this study, with 140 participants in both the FSM group and the SM group.

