## Statistical methods

### Statistical methods for primary and secondary outcomes {20a}

SPSS V26 (IBM Corp., Armonk, NY, USA) will be used for both data input and analysis. Statistical analysis will be performed as follows. First, descriptive statistics will be used for all outcome measures at each measurement point to summarize the results. For normally and nonnormally distributed measurement data, the mean ± standard deviation, and median, will be used for the statistical description of the degree of trend, and dispersion, respectively. Second, differences in the mean change in primary and secondary outcomes from baseline to each time point between the groups will be compared using two independent samples *t*-tests or the Mann–Whitney *U*-test. Finally, chi-square tests will be used for blind evaluation. Statistical significance will be set at a *p*-value < 0.05 (two-sided). Table 3 summarizes the statistical analysis of primary and secondary outcomes.

**Table 3 Tab3:** Variables, measures, and methods for statistical analysis of primary and secondary outcomes

Variable/outcome	Outcome measure	Methods of analysis
1) Primary		
The mean of change in shoulder function from baseline to 4, 12, 18, and 24 weeks	Constant-Murley score (continuous)	*T*-test or Mann–Whitney *U*-test^a^
2) Secondary		
The mean of change in shoulder pain from baseline to 4, 12, 18, and 24 weeks	Visual analogue scale (continuous)	*T*-test or Mann–Whitney *U*-test^a^
The mean of change in shoulder range of motion from baseline to 4, 12, 18, and 24 weeks	Active range of movement of shoulder joint (continuous)	*T*-test or Mann–Whitney *U*-test^a^
The mean of change in quality of life from baseline to 4, 12, 18, and 24 weeks	The 36-Item Short Form Survey (continuous)	*T*-test or Mann–Whitney *U*-test^a^

^a^For data conforming to normal distribution, *T*-test is used, and for data not conforming to normal distribution, Mann–Whitney *U*-test test is used

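### The 104 per group and 90% power are calculated for superiority by a margin of 5.95 CMS points, but the planned analysis tests a zero difference, so the stated power is not that of the planned test

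*Protocol article*

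**What the plan says.** **Sample size {14}.** The inputs come from a preliminary study of CMS change over the 4-week treatment. For the active arm it reports that "CMS increased by 24.32 (μ_r_) in the FSM group". The mean gain under sham (μc) was 10.31. The spread is taken from one arm only: "the standard deviation of the FSM group was 17.84". The section then sets Δ, "when 1/3 of the standard deviation of the FSM group is selected for Δ". The error rate is one-sided 0.025, the power 90% and the allocation 1:1. The printed formula has the square of (μr − μc − Δ) in its denominator, and the result is given as 104 per group. Allowances for dropout and for the three centres bring this to 140 per group, 280 in all.

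**Statistical methods {20a} and Table 3.** For the primary outcome, "differences in the mean change in primary and secondary outcomes from baseline to each time point between the groups will be compared" by a two-sample t-test or, if the data are not normal, a Mann–Whitney U-test. Significance is p < 0.05, two-sided. No margin, shifted null or confidence-interval criterion is given.

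**Elsewhere.** Trial design {8} speaks only of superiority. Table 1 gives the metric as the between-group difference in mean change. Δ does not appear outside the sample-size section.

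**The concern.** Subtracting Δ from the expected difference is how one sizes a test of the null hypothesis that the benefit is no greater than Δ. Δ cannot be the expected effect, because μr − μc already fills that place in the formula. The test in the analysis section has a different null hypothesis, that of no difference. Two parts of the same protocol therefore describe two different tests, and the power printed for one is left to stand for the other.

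Two things follow. The 90% misdescribes what the trial can detect with its planned test. And because nothing explains Δ, a reader of the sample-size section may take a significant result as evidence of a benefit above 5.95 points, which the planned test does not address.

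**Working it through.** **Inputs, all from Sample size {14}:** μr = 24.32; μc = 10.31; σ = 17.84 (FSM group, used for both groups); Δ = σ/3; Z values 1.96 and 1.282; K = 1.

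- Expected difference: 24.32 − 10.31 = 14.01
- Δ = 17.84/3 = 5.947
- Difference net of Δ: 14.01 − 5.947 = 8.063

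**1. Reproduce the plan's figure.**
n = (1.96 + 1.282)² × 17.84² × 2 / 8.063² = 10.511 × 318.27 × 2 / 65.01 = 102.9, so 103 per group. With the t distribution, 104 per group gives power 0.900 for the margin test. The stated 104 is reproduced when Δ is subtracted.

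**2. The same inputs for the planned test (null difference zero).**
n = 10.511 × 318.27 × 2 / 14.01² = 6690.3 / 196.28 = 34.1, so 35 per group by the normal formula. With the t distribution, 35 falls just short (power 0.899) and 36 gives 0.908. At 104 per group, power for a true difference of 14.01 is 0.9999.

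**3. What the planned t-test can detect with 90% power.**
At 104 per group the standard error is 17.84 × √(2/104) = 2.474. Power for a true difference of 8.06 is 0.900. This is the margin calculation with the null shifted back to zero.

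**4. Observed difference at which each test becomes significant (SD 17.84).**

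| Analysed per group | Standard error | t critical value | Zero-difference test | Margin test (add 5.95) |
|---|---|---|---|---|
| 104 | 2.474 | 1.972 | 4.88 | 10.82 |
| 140 | 2.132 | 1.969 | 4.20 | 10.14 |

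104 is the protocol's calculated requirement, and 140 is everyone enrolled. Across that range the planned test reaches significance below 5.95 points, whereas a margin test would need an observed difference above 10.

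**5. Sidedness.** One-sided 0.025 and two-sided 0.05 share the critical value 1.96 in the direction of benefit. The disagreement lies in the null value, not in the number of sides.

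**The case against.** The best defence is that nothing goes wrong with the trial's inference. Tested against zero, the trial has far more than 90% power at the assumed difference, and its 5% type I error for the hypothesis of no difference is untouched. Numerically, 104 per group is also what a conventional sizing for 8.06 points would give, so Δ could be seen as a cautious reduction of the preliminary estimate. The protocol never calls Δ a margin, a minimum important difference or a success criterion. Its stated aim and hypothesis (efficacy, and faster improvement than with sham) fit a test against zero.

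All of that stands, and it limits the point. A reader might infer that the trial is underpowered; step 2 shows the opposite. A reader might also infer that it will declare false successes, because it can be significant when the true benefit is only Δ. With 104 to 140 analysed per group, that probability is about 67% to 79%. But if the true benefit is 5.95 points, rejecting no difference is correct. The figure is power, and should not be set beside the 2.5% error rate of a test that is not planned. Nor do the documents support saying that the trial breaks a success criterion of its own, because no section commits it to one.

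The defence does not remove the mismatch. Δ is not described as a cautious reduction either, and the power statement still does not describe the planned test. A separate statistical analysis plan may add detail, but the article itself already fixes the test and the significance level. This is a conflict between two stated elements, not an omission.

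**Conclusion.** The point holds as a mismatch between the hypothesis sized and the hypothesis tested. The 104 per group and 90% power belong to a test of benefit above 5.95 CMS points; the planned test is of zero difference. On the protocol's inputs the planned t-test needs about 36 per group, roughly a third of 104, and at 104 its power for 14.01 points is over 99.9%. A significant result shows a difference from sham, not superiority by Δ.

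The figures assume a common SD of 17.84, the preliminary difference of 14.01, and the t-test; the Mann–Whitney option was not calculated. That Δ acts as a margin is read from the formula, since the protocol does not say so. The validity of the planned test is not in question.

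**What to change.** **Main change, in Sample size {14}.** Keep 280 participants and the zero-difference test. Remove Δ and restate the calculation, for example: *With 104 evaluable participants per group, a two-sided 0.05 t-test has 90% power for a true difference in CMS change of 8.06 points (SD 17.84) and over 99.9% power for the 14.01 points seen in the preliminary study. A significant result shows a difference from sham, not superiority by 5.95 points.*

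**Only if a margin claim was intended.** Leave the formula and change Statistical methods {20a} and Table 3 before unblinding:

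- Fix the margin in CMS points and justify it clinically; the article gives no basis for 5.95 beyond a third of one group's SD.
- Require the lower limit of the two-sided 95% confidence interval for the mean CMS difference to exceed that margin.
- Name the principal time point at which this applies. Table 1 lists 4 and 12 weeks, and the preliminary data cover 4 weeks only.
- Use an analysis of the mean difference in place of the Mann–Whitney option, which does not estimate it.

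**Cost.** The main change is wording only; enrolment, randomisation and the planned test stay as they are. The alternative is a stricter success criterion: with 104 to 140 analysed per group and a 5.95-point margin, an observed difference of about 10.1 to 10.8 points would be needed. That is a design decision for the sponsor.

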### Recruitment {15}

Recruitment posters for the study will be posted at the three trial centers, and recruitment advertisements will be posted on the hospitals’ official WeChat accounts. Additionally, doctors at each trial center will inform patients who are assessed for shoulder pain about the study.

## Assignment of interventions: allocation

### Sequence generation {16a}

Eligible participants will be randomly assigned at a 1:1 ratio to either the FSM group or the SM group. The randomization scheme and allocation sequence will be generated via SAS PROC PLAN software (SAS Inc., Cary, NC, USA) by the Shanghai Medical Clinical Research Center (an independent third-party institution). The randomization list will be stratified by study center and will comprise the code, randomization number, and treatment regimen.

#### Concealment mechanism {16b}

The randomization list will be administered by the randomization manager who will not participate in other study procedures, and outcome assessors, data analysts-blinded and patients will be blinded to the randomization list.

#### Implementation {16c}

The randomization list will be generated by Shanghai Medical Clinical Research Center and submitted to the randomization manager for storage. Upon participant enrollment, the therapist will obtain the randomization number and treatment regimen for the patient via phone or WeChat, which will not be known by the patients and outcome assessors.

## Assignment of interventions: blinding

### Who will be blinded {17a}

Participants, outcome assessors, and data analysts will be blinded to the treatment allocation. To assess the effectiveness of the blinded approach, the participants and outcome assessors will answer a question at the week 12 evaluation point related to the allocation (“In your opinion, which intervention did you receive?”). The possible answers are as follows: (1) positive intervention; (2) sham intervention; or (3) I have no idea.

### Procedure for unblinding if needed {17b}

This study defines three unblinding situations: (1) when data entry is completed, (2) when statistical analysis is completed, and (3) when serious adverse events occur. All adverse events will be reported to the data and safety monitoring committee (DSMC), who will decide whether the patient’s participation needs to be discontinued and whether the patient should be unblinded immediately.

## Data collection and management

### Plans for assessment and collection of outcomes {18a}

Validated questionnaires and physical examinations were used to evaluate outcomes (Table 1).

The collection and recording of details of the chief complaint, demographics, clinical diagnosis, and details of medical and surgical history is the responsibility of the lead researchers.

Trained independent outcome assessors will be located at each study center. Before the start of the study, outcome assessors will receive standardized training to clarify their responsibilities and master the method of outcome evaluation. They will be responsible for collecting and recording symptoms using the methods listed in Table 1 and will be asked not to actively learn about patient groupings and interventions.

Patient-determined outcomes which include VAS [17], SF-36 scores [19], and CMS [16] will be self-reported by the patients, while ROM [18] and strength will require a standardized physical examination and recording by the research assistants. The effectiveness of the blinding will be assessed by research assistants who will ask questions and record the results at week 12. Adverse events, possible causes, whether the patient’s participation in the study is discontinued, and unblinding will also be recorded in detail by the research assistants.

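### The role that examines ROM and strength is also told to collect the week-12 treatment guess, the text conflicts on who measures, and the one blinding question printed does not fit outcome assessors

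*Protocol article*

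**What the plan says.** **Who measures.** The section on assessment and collection of outcomes {18a} states that "ROM [18] and strength will require a standardized physical examination and recording by the research assistants". The CMS section adds: "The research assistants assist the participants in completing the items and obtaining the final score". An earlier paragraph of {18a} says of the trained independent outcome assessors: "They will be responsible for collecting and recording symptoms using the methods listed in Table 1". Table 1 lists the CMS and ROM. Trial design {8} likewise makes independent assessors responsible for the outcomes. {18a} also counts the CMS among the self-reported measures.

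**Who collects the guess.** The sentence in {18a} that follows the ROM and strength assignment reads: "The effectiveness of the blinding will be assessed by research assistants who will ask questions and record the results at week 12".

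**What is asked, and of whom.** Under Who will be blinded {17a}, "the participants and outcome assessors will answer a question at the week 12 evaluation point related to the allocation". The only wording given is "In your opinion, which intervention did you receive", with the options "1) positive intervention; (2) sham intervention; or (3) I have no idea". The statistical methods section {20a} plans chi-square tests on the blinding data.

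**When outcomes are scored.** Assessments are at baseline and weeks 4, 12, 18 and 24. Table 1 places the principal CMS analysis at weeks 4 and 12, and Table 3 tests CMS change at all four post-baseline visits.

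**The concern.** A measurer who has just recorded that a participant believes the treatment was real, or sham, has information that can colour a later goniometer reading or strength test. This holds even if the measurer does not know the allocation. It is a separate question from whether measurers are blinded at the start.

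Two things are at stake. One is the independence of the examined part of the primary outcome once the guess has been collected. The other is whether the planned check of assessor blinding can be read. The trial describes itself as assessor-blinded in its abstract and design section, and the week-12 question is the only test of that claim the article describes.

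**Working it through.** **1. Role against task.**

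| Task | Research assistants | Outcome assessors |
|---|---|---|
| Collect outcomes listed in Table 1 (CMS, ROM and others) | – | {8}; {18a}, earlier paragraph |
| Examine and record ROM and strength | {18a}, later paragraph | ROM, through Table 1 |
| Help complete the CMS and obtain its score | CMS section | CMS, through Table 1 |
| Ask and record the week-12 guess | {18a} | – |
| Answer the week-12 question | – | {17a} |

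Two readings are possible. If research assistants are the outcome assessors, the assessors collect the participants' guesses. If they are different people, the article gives the same measurements to both groups. Either way the text needs correcting.

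**2. Share of the primary outcome that is examined.** The CMS section gives pain 15, daily living 20, strength 25 and ROM 40, and 15 + 20 + 25 + 40 = 100 as stated. The examined part is 25 + 40 = 65 points. The description of the CMS in {18a} as self-reported therefore does not fit most of its points.

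**3. Visits exposed, if the same people do both tasks.**
- Week 4: scored before the question exists, so not affected.
- Week 12: affected only if the question is put before the examination. The article does not give the order.
- Weeks 18 and 24: scored after the guess is known, so exposed.

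Of the two principal time points, one is safe and the other is conditional.

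**4. Possible size (illustration only).** The plan gives no figure for this. Suppose a measurer shifts the score by *b* points towards the guess, every participant guesses, and a guess is right with probability *p* in both arms. The mean shift is +*b*(2*p* − 1) in the FSM arm and −*b*(2*p* − 1) in the sham arm, so the bias in the difference is 2*b*(2*p* − 1).

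- *b* = 1, *p* = 0.6: 2 × 1 × 0.2 = 0.4 points
- *b* = 2, *p* = 0.7: 2 × 2 × 0.4 = 1.6 points
- *b* = 3, *p* = 0.8: 2 × 3 × 0.6 = 3.6 points

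For scale, 140 per arm less the planned 20% dropout is 140 × 0.8 = 112. With the stated SD of 17.84, the standard error of the difference is 17.84 × √(2/112) = 2.38, and 1.6 / 2.38 = 0.67 standard errors.

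Both *b* and *p* are assumptions. If a fraction *u* of participants in each arm has no opinion, the bias is multiplied by (1 − *u*). If guesses are no better than chance (*p* = 0.5), it is zero. The SD comes from the FSM group of the preliminary study over 4 weeks, so applying it to later visits is a further assumption.

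**5. The question.** Its wording addresses the person treated. An assessor receives no intervention, so the wording fails for that respondent, although the three answer options would serve. An assessor who has seen the participant's answer could also simply repeat it, and the chi-square test on assessor answers would then say little about the assessor's own blinding.

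**The case against.** The best case on the other side has four parts.

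- **A role is not a person.** Research assistants appear throughout the article: appointments and diary cards, examinations, adverse events, data entry. Nothing says that one individual both measures and asks, or returns at weeks 18 and 24. If independent assessors measure and assistants only ask, the route to bias closes. This stands, and it is why the point is conditional. It does not remove the point, because {18a} assigns both tasks to one role in consecutive sentences. Where the article wants separate people it says so, as in Data management {19}, which has two independent assistants entering data.
- **Visit order belongs in the full protocol or CRF.** This also stands. The missing order is not raised as an omission; it only limits what can be said about week 12.
- **A belief is not the allocation.** This stands. A reader might infer that the blinding check unblinds the measurers. The article does not support that: the answer may be wrong, or may be that the participant has no idea.
- **The question is an editorial slip.** This largely stands. A reader might conclude that the assessor check would yield no usable data. That goes too far, since the answer options fit and an assessor could guess what was meant. The wording should still be put right before data are collected with it.

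**Conclusion.** The point holds as an unreconciled assignment of roles that leaves open an avoidable route to bias, together with a question that does not fit one of its two groups of respondents. The exposure covers weeks 18 and 24 if the same people measure and ask, and week 12 only if the question also comes before the examination. Week 4 is unaffected.

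The examined part is 65 of the 100 CMS points. The size of any bias is unknown. The 0.4 to 3.6 point range rests on assumed inputs, ignores participants without an opinion, and should not be quoted as an estimate. A reader might infer that the principal result is compromised, or that the same individuals must perform both tasks. The article establishes neither. The change is worth making because it is cheap and protects a blinding claim on which the trial relies.

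**What to change.** 1. In Trial design {8}, the CMS section and {18a}, state consistently who measures ROM and strength and who scores the CMS, and correct the description of the CMS as self-reported.
2. In {17a} and {18a}, have participants complete the guess themselves after all week-12 measurements, seal it, and keep it unopened until follow-up ends. No measurer then sees it, whoever that person is.
3. In {17a}, give outcome assessors a separate item for each participant: *Which intervention do you think this participant received?* They complete it after their own week-12 scoring and without seeing the participant's answer. The existing answer options can stay.

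The cost is minor CRF rewording and envelope handling at three centres. Because the slip is self-completed and stays sealed, no extra staff are needed, and there are no added visits or participants.
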